### Evaluation

Evaluation of the Life Now Exercise program involves measures of uptake, safety, adherence and effectiveness of the program. These analyses incorporate elements of the RE-AIM (reach, effectiveness, adoption, implementation and maintenance) framework [31]. Evaluation of the effectiveness of the program involves comparisons among pre-program, post-program and 6 months follow-up assessments. The evaluation will be undertaken on a sample of 600 people with cancer participating in the program (refer sample size calculations below) with data collection initiating in 2011 and proceeding until the target sample size is achieved.

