#### Statistical analyses

Data will be analysed using an intention-to-treat approach with maximum likelihood imputation of missing values. Analyses will include standard descriptive statistics, Student’s *t*-tests, chi-square, correlation, regression and repeated measures ANOVA (or ANCOVA as appropriate) to examine differences over time. Clinically relevant covariates will be included in analyses. Sub-group analyses based on cancer site and anti-cancer treatment status will be conducted. Investigations into responders and non-responders will be conducted to explore heterogeneity of intervention effect.

Sample size calculations were based on having sufficient power to detect a small effect (*d* = 0.02) in study endpoints. Given the number of planned assessments, correction for multiple testing is required. An alpha level of 0.001 was applied which provides adjustment for up to 50 tests. A priori, 420 participants are required to achieve 80% power at an alpha level of 0.001 (two tailed) to demonstrate a mean paired difference of *d* = 0.02 from pre- to post-program. To ensure sufficient participant numbers at the completion of the Life Now Exercise program, sample size calculations accounted for a 30% attrition rate. Thus the evaluation will be conducted on a sample size of 600 participants.

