
There are important limitations to note in the design and evaluation of the Life Now Exercise program. As participants self-enrol into the program they will have a level of motivation to undertake exercise that may not be representative of all people with cancer. Integrating systematic referral of all people with cancer through oncology departments and treatment centres is not possible within the scope of this study. While program sites span metropolitan and regional areas, the program is implemented in Western Australia only and limited to the context of the Australian health care system. Program participation is funded by Cancer Council Western Australia so as to be delivered at no cost to people with cancer. These factors may limit the generalizability for implementation as an on-going program in other settings. Evaluation of the program is limited by the single-group design which precludes appraisal against a comparable sample of people with cancer. Evaluation is also limited by the reliance on community-based health professionals to administer assessments and return program documentation to the research team. Assessor bias cannot be ruled out as the same health professional who delivered the intervention administered the objective assessments (note: patient reported outcomes were conducted independently by the participant). The potential influence of social support on exercise motivation and behaviour may not be adequately assessed by domains of the Theory of Planned Behaviour questionnaire. These limitations are offset by strengths to the implementation and evaluation of the Life Now Exercise program. The program incorporates theory based behaviour change strategies and applies evidence based practice in the delivery of exercise to people with cancer. External validity of the program is supported by the implementation within a community-based setting to people with any diagnosis of cancer. This is further enhanced by administering the program as a “real-world” intervention delivered in a standard supportive care service setting. Evaluation of the program is guided by the RE-AIM framework and includes a robust suite of endpoints.

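### The sample size is justified on d = 0.02, but 420 completers have about 0.2% power for that effect, not 80%; the figure of 420 fits d = 0.20

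*Protocol article*

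**What the plan says.** The sample-size paragraph in the protocol article (Methods/Design, Evaluation, Statistical analyses) sets out a full chain of inputs.

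- Target effect, first mention: "sufficient power to detect a small effect (*d* = 0.02) in study endpoints".
- Multiplicity: "An alpha level of 0.001 was applied which provides adjustment for up to 50 tests".
- Completers, power and sidedness: "420 participants are required to achieve 80% power at an alpha level of 0.001 (two tailed"), and the same sentence ends with the effect to be shown, "to demonstrate a mean paired difference of *d* = 0.02 from pre- to post-program".
- Attrition: "sample size calculations accounted for a 30% attrition rate".
- Result: "the evaluation will be conducted on a sample size of 600 participants".

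The opening paragraph of the Evaluation section gives the same target of 600 and refers the reader to this calculation for its justification. The Discussion confirms that there is no comparison group: "Evaluation of the program is limited by the single-group design". The calculation is therefore for a within-person change from before to after the program. No other part of the article gives a different effect size.

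**The concern.** A standardised difference of 0.02 is one fiftieth of a standard deviation. At a two-sided alpha of 0.001, a few hundred pairs cannot detect so small a change. The article nevertheless calls the effect small and attaches 80% power to it with 420 pairs. Required n varies with 1/d², so an error of a factor of 10 in d is an error of a factor of about 100 in n.

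Two things are at stake. First, this is the only power statement in the article and the only reason given for enrolling 600, and it cannot be reproduced from its own inputs. Second, it misstates what the study can detect. A reader who takes it at face value would believe that changes of 0.02 SD are within reach on up to 50 tests, and could read a non-significant endpoint as evidence against changes far smaller than the study can see.

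**Working it through.** **Inputs, all from the Statistical analyses section:** d = 0.02; two-sided alpha 0.001; power 80%; 420 completers; 30% attrition; 600 enrolled. The single-group design (Discussion) makes a paired t-test the applicable model.

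**Steps that reproduce**

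- Alpha: 0.05 / 50 = 0.001.
- Attrition: 420 / (1 − 0.30) = 600.

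**Required number of pairs**

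Normal approximation: n = (z₁₋α/₂ + z_power)² / d², with z values 3.2905 and 0.8416. The squared sum is about 17.0746.

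- d = 0.02: 17.0746 / 0.0004 gives 42,687.
- d = 0.20: 17.0746 / 0.04 = 426.9, so 427.

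Exact calculation, using the non-central t distribution with n − 1 degrees of freedom and non-centrality d√n:

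| d | Pairs for 80% power | Enrolled at 30% attrition |
|---|---|---|
| 0.02 (as printed) | 42,693 | 42,693 / 0.70 = 60,990 |
| 0.20 | 433 | 433 / 0.70 = 618.6, so 619 |

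At the printed effect, the requirement is 42,693 / 420 ≈ 102 times the stated figure.

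**Power at the stated number (exact t, two-sided alpha 0.001)**

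| Pairs | d | d√n | Power |
|---|---|---|---|
| 420 | 0.02 | 0.41 | 0.21% |
| 600 (no attrition) | 0.02 | 0.49 | 0.26% |
| 420 | 0.20 | 4.10 | 78.3% |
| 433 | 0.20 | 4.16 | 80.1% |

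The smallest d with 80% power at 420 pairs is 4.1321 / √420 = 0.202 by normal approximation and 0.203 by exact t.

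**Other readings of d = 0.02**

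- One-sided alpha 0.001: 38,654 pairs.
- Two-sided alpha 0.05 (no multiplicity correction): 19,625 pairs; power at 420 is 6.9%.
- One-sided alpha 0.05: 15,458 pairs.
- d scaled by the SD of the raw scores, with pre-post correlation r: the paired effect is 0.02 / √(2(1 − r)). Power at 420 is 0.21% at r = 0.5 and 0.87% at r = 0.9. The paired effect reaches 0.20 only at r = 0.995, since 0.02 / √0.01 = 0.20. The article states no such correlation.

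None of these brings d = 0.02 near 420 pairs.

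**The case against.** The strongest reply is that this is a decimal slip in the write-up and not a fault in the design. The article calls the effect small, d = 0.20 gives 427 pairs by normal approximation against 420 stated, and the alpha and attrition steps are right. On that reading enrolment, endpoints, alpha and analysis are unaffected. This is the most plausible explanation, and it is why the remedy leaves 600 alone. It does not make the printed statement true. The figure appears twice, and a reader cannot settle from the text which input is wrong.

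It can also be said that the shortfall from 80% at d = 0.20 is trivial: 79.1% by normal approximation, 78.3% by exact t, with no method named. That stands as a comment on size. It is a side point, and it disappears if attrition is a little lower: 433 of 600 completing is 72.2%, or 27.8% attrition.

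The plan also intends maximum likelihood handling of missing values, so a completers-only t-test only approximates the planned analysis. This is fair but does not help, because even 600 complete pairs give 0.26% power at d = 0.02.

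Finally, the article sets no rule for interpreting null results, so over-reading them is a risk and not something it plans. That is correct. The firm part of the harm is that the only justification for n is false as printed and overstates the study's sensitivity.

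**Conclusion.** The concern holds. At the printed effect of d = 0.02, power with 420 completers is 0.21% against the stated 80%, and the required number is about 42,690 against 420. The printed effect is about ten times smaller than the smallest one the study can detect with 80% power (0.203). The result assumes a paired t-test, two-sided alpha 0.001 and d standardised by the SD of the change; the alternatives tried on alpha and sidedness, and any realistic pre-post correlation, leave the conclusion unchanged.

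That 0.20 was the value used is an inference from how nearly it reproduces 420, and the sponsor needs to confirm it. If it is right, the target of 600 is about adequate and the remaining gap is under two percentage points of power. The correction must still be made, because the statement is the sole stated basis for the sample size.

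**What to change.** 1. Check the original calculation for the effect size entered. If it was 0.20, replace 0.02 by 0.20 in both sentences of the sample-size paragraph.
2. State that d is the mean change divided by the SD of the change.
3. Restate the power in one of two equivalent ways: 420 completers give 78% power at d = 0.20, or 420 completers give 80% power for d = 0.203 (both paired t-test, two-sided alpha 0.001).
4. Keep the target of 600. The reference to it in the Evaluation section then needs no change.

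If 0.02 really was the intended effect, changing the wording is not enough: about 60,990 people would have to be enrolled, so the claim to detect that effect would have to be withdrawn.

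The cost is two corrected numbers, a short definition and a slightly less favourable power figure. No additional participants or assessments are needed.

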## Discussion

Clinical research has established appropriate exercise as an effective adjunct therapy for people with cancer [9–11, 15], oncology organisations have identified the importance of incorporating exercise in cancer care [15–17] and people with cancer have indicated their wish to participate in appropriately designed and delivered exercise programs [24, 25]. However, information regarding effective approaches to incorporate exercise into routine care is limited. A major challenge is to translate knowledge of efficacious exercise interventions into practice with feasible, scalable and sustainable programs that are generalizable for all people with cancer. The Life Now Exercise program has been developed to bridge the gap between research and practice, and generate data to help guide implementation strategies/models for the integration of exercise in the cancer care paradigm.

Research involving people with cancer has demonstrated that motivational outcomes are strong predictors of exercise behaviour [30]. Thus the design of the Life Now Exercise program is theoretically based on the determinants of exercise motivation and behaviour among people with cancer. The most widely used theoretical model in cancer (Theory of Planned Behaviour; TPB) suggests that people with cancer will intend and be motivated to exercise when they: 1) view it positively; 2) believe that people important to them think they should exercise; and 3) believe that exercise is under their control and they are able to perform exercise [29]. Constructs of the TPB have been reported as statistically significant predictors of the intention to participate in exercise [41, 42] and to significantly predict program attendance [42], although the strength of these predictions are moderate [43]. While limited information exists about how to use these constructs to develop interventions that enhance positive exercise behaviours, current knowledge suggests that addressing patients attitudes towards exercise, their subjective norm and perceived behavioural control are critical components of an effective exercise program [30]. Additionally, social support/social connectedness provided by bringing together peers has been identified as a key determinant of adherence to exercise programs and represents another component critical to the design of effective exercise programs [30, 44]. Furthermore, investigation of barriers to exercise among people with cancer has identified a variety, most common of which are disease specific (e.g., treatment-related side effects, especially fatigue) and factors common to non-cancer adults (e.g., time constraints, distance/travel time, weather extremes). Additional barriers include issues such as lack of facilities for people with cancer and safety concerns [24, 25]. Commonly identified facilitators of exercise in people with cancer include appropriate supervision, group based but individually tailored and gradually progressed exercise prescription [24, 25, 45]. The inclusion of feedback and approval from their oncologist or general physician were factors also identified to facilitate continued exercise participation [24, 25]. Application of the TPB constructs and common exercise barriers and facilitators led to program components within the Life Now Exercise program. Specifically, requiring the endorsement of oncology specialist or general physician for participation in the intervention underscores the positive value of exercise behaviour and indicates their support for exercise (as well as screening for contraindications to exercise). Upskilling of exercise physiologists allows for targeted education of patients, the ability to tailor the exercise prescription and progression to each individual and modify the prescription to manage treatment-related side effects, all of which helps allay potential concerns about safety of the intervention. Administration of the exercise program within local community-based exercise clinics enhances patients’ perceived behavioural control and limits common barriers of distance from and travel time to exercise facilities. The positive atmosphere of this environment coupled with the group-based setting may also contribute to enhanced affective attitude and subjective norm within people with cancer. Furthermore, the social support and connectedness provided by bringing together a group of people with the shared experience of cancer may facilitate adherence to the program and continuation of positive exercise behaviours longer-term. The incorporation of program elements addressing constructs of behaviour change theory, barriers and facilitators to exercise, combined with exercise physiologists’ use of evidence based practice, is designed to maximise engagement of, and potential benefits to, people with cancer.

Information arising from the implementation of the Life Now Exercise program extends existing reports of community-based exercise programs for people with cancer designed for ongoing operation [46–49]. The ‘Livestrong at the YMCA’ program operates at over 400 sites throughout America [50]. The program involves 12 weeks of twice weekly group based exercise sessions administered at YMCA facilities by personal trainers and the benefits of participation have been reported on a sample of 187 participants [47]. The ‘FitSTEPS for Life’ program operates across various community based exercise sites (e.g., community centres, churches, health centres) in Texas, USA where people with cancer receive an individualised exercise plan and are provided access to ongoing exercise supervision [51]. Improvements in a range of quality of life domains were observed following 2 years of involvement in the program on a sample of 177 participants [46]. Cancer specific community-based exercise programs have also been developed in Canada. The ‘CanWell’ program is a 12-week exercise (two supervised sessions weekly) and education program administered by staff trained in program delivery at a YMCA facility in Ontario. Evaluation of a sample of 65 participants demonstrated improvements in quality of life and physical function at the completion of the program [49]. The BEAUTY program (*Breast* cancer patients *E*ngaging in *A*ctivity while *U*ndergoing *T*reatment) is a 12-week program involving twice weekly group based exercise sessions and biweekly education sessions delivered by certified exercise physiologists at a single tertiary exercise facility in Alberta [52]. Evaluation was undertaken on a sample of 80 patients which demonstrated safety but no clinically significant improvements following program completion (possibly associated with the low attendance rate of ~30%) [48]. These data provide promising initial evidence of the effectiveness of cancer specific exercise programs implemented in the community but significant continued effort is required to increase knowledge translation and implementation approaches. Evaluation of the Life Now Exercise program extends existing reports by assessing the effectiveness of a community-based exercise program in the largest sample of people with cancer to date (*n* = 600) using a comprehensive suite of assessments. The sample size and inclusive participant criterial allows for sub-group analyses which may provide insight into how people with different cancer types and treatment status respond to exercise. Importantly, examination of which participants do and don’t respond to exercise will provide novel information regarding demographic, clinical, motivational and other characteristics/factors that influence the response to exercise in people with cancer. Further to this, the evaluation will provide insight into what kind of participants engage in a community-based exercise program which may help inform future work to target people with cancer who require additional stimulus to engage in positive exercise behaviours. Examination of the cost-effectiveness of the program represents a unique addition to the literature and significant advance in current knowledge regarding the potential value of cancer-specific exercise interventions to the health system. Additionally, detailed reporting of the elements contributing to the design and implementation of the Life Now Exercise program may help inform the development of feasible, effective and sustainable supportive care exercise services. Collectively this information will help guide future research and translational work addressing the low levels of exercise behaviour in people with cancer.

There are important limitations to note in the design and evaluation of the Life Now Exercise program. As participants self-enrol into the program they will have a level of motivation to undertake exercise that may not be representative of all people with cancer. Integrating systematic referral of all people with cancer through oncology departments and treatment centres is not possible within the scope of this study. While program sites span metropolitan and regional areas, the program is implemented in Western Australia only and limited to the context of the Australian health care system. Program participation is funded by Cancer Council Western Australia so as to be delivered at no cost to people with cancer. These factors may limit the generalizability for implementation as an on-going program in other settings. Evaluation of the program is limited by the single-group design which precludes appraisal against a comparable sample of people with cancer. Evaluation is also limited by the reliance on community-based health professionals to administer assessments and return program documentation to the research team. Assessor bias cannot be ruled out as the same health professional who delivered the intervention administered the objective assessments (note: patient reported outcomes were conducted independently by the participant). The potential influence of social support on exercise motivation and behaviour may not be adequately assessed by domains of the Theory of Planned Behaviour questionnaire. These limitations are offset by strengths to the implementation and evaluation of the Life Now Exercise program. The program incorporates theory based behaviour change strategies and applies evidence based practice in the delivery of exercise to people with cancer. External validity of the program is supported by the implementation within a community-based setting to people with any diagnosis of cancer. This is further enhanced by administering the program as a “real-world” intervention delivered in a standard supportive care service setting. Evaluation of the program is guided by the RE-AIM framework and includes a robust suite of endpoints.

There is a dearth of knowledge regarding effective approaches of translating exercise oncology evidence into cancer care. To bridge the gap between research and practice, the Life Now Exercise program was designed and implemented to provide people with cancer access to evidence based exercise medicine. The framework for program implementation and evaluation offers insight into the development of feasible, sustainable and potentially effective supportive care services involving exercise. Effective community-based exercise programs specifically designed for people with cancer may help reduce the disease burden of cancer and improve the health and wellbeing of people with cancer through increased adherence with exercise guidelines.

## Abbreviations

BSI-18: Brief Symptom Inventory-18
DXA dual: energy X-ray absorptiometry
FACIT-Fatigue: Functional Assessment of Chronic Illness Therapy-Fatigue
ICER: Incremental cost-effectiveness ratio
QALY: quality adjusted life years
QLQ-C-30: European Organisation for Research and Treatment of Cancer
RE-AIM: Reach, effectiveness, adoption, implementation and maintenance
RM: Repetition maximum
RPE: Ratings of perceived exertion
SF-36: Medical Outcomes Study 36-Item Short-Form Health Survey
TPB: Theory of Planned Behaviour
VO_2_peak: Peak oxygen consumption
YMCA: Young Men’s Christian Association
